#### *Secondary analyses*

Secondary analyses will be conducted to examine differences between groups in terms of derived weight indices (i.e. mean weight-for-age Z score and proportion of underweight), length (mean length gain, length-for-age Z score and proportion of stunting), cognitive and motor development (mean score) and STH prevalence and intensity. Means will be compared using a one-way ANOVA procedure and proportions will be compared using chi-square statistics. Adjustment for imbalances among measured determinants and risk factors will be conducted as needed, using multivariate linear or logistic regression for continuous and dichotomous outcomes, respectively. Length-for-age and weight-for-age Z scores will be calculated using the WHO Anthro software (Version 3, 2009), which compares growth in the study population to a WHO standard population. In addition to age, this method also takes into account the sex of the child. Cut-offs used to categorize the continuous variables of weight, length and eggs per gram are based on WHO standards for underweight (<-2 SD), stunting (<-2 SD) and STH intensity (low and moderate/heavy, according to parasite-specific egg counts), respectively.

To evaluate the possible modification of baseline anthropometry on the effect of deworming, multivariate regression models (e.g. linear for continuous variables and logistic for dichotomous outcomes) will be used with baseline weight and length included as interaction terms. This analysis is included to document the added value of deworming among young children who are already faltering. It will provide insight into both the preventive nature of deworming and also into whether deworming can reverse growth faltering that has already occurred by 12 months of age. Finally, possible intra-cluster correlation (by health centre), will be investigated using the intraclass correlation coefficient. If clustering is indeed detected, hierarchical logistic regression models will be used to obtain accurate estimates of treatment effects.

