### **Study community**

The study will be conducted in neighbouring districts around the city of Iquitos, the capital of the Loreto region in the Peruvian Amazon. Three districts of extreme poverty have been identified (Belén, Punchana and San Juan) where worm infections are highly endemic and malnutrition prevalence is high. The prevalence of underweight in children 12 to 14 months of age was recently estimated to be 31% and STH prevalence to be 29% ([name] et al, manuscript under review). The STH prevalence doubles by 18 months of age ([name], unpublished data) and reaches over 85% in school-age children. Previous research in the area has shown a significant association between STH infection and poor growth in both preschool- and school-age children ([name] et al, manuscript under review). Both STH infections and malnutrition have been identified as priority concerns by stakeholders in the community. At present, there is no routine deworming for preschool-age children.

Preschool-age children attend routine government-sponsored CREDE visits at health clinics in Peru once-monthly from birth to 12 months of age, and every two months from 12 to 24 months of age (with less frequent visits continuing through preschool-age). Each health centre has one to two nurses who are responsible for CREDE check-ups. During routine CREDE visits, anthropometric measurements (e.g. weight and length) are taken, developmental milestones are recorded (e.g. gross motor skills), and children receive routine age-appropriate immunizations and supplements. Parents also receive nutrition and other health counselling for their child.

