### **Outcome measurements**

Prior to randomization, a baseline assessment will be conducted which will include anthropometry, and cognitive and motor development. A questionnaire will be administered to the child's mother to obtain socio-demographic information, medical history, feeding practices, and environmental exposure history. Stool specimens will be collected from all children (a small amount of fruit may be given to children, as needed, to facilitate a bowel movement. This method has been used successfully in the past and does not interfere with the quality of the stool). Follow-up assessments will be made at the 18-month CREDE visit, and at the 24-month CREDE visit, at which time all measurements will be repeated.

The primary outcome will be the mean weight gain between the 12 and the 24-month visit. Weight will be measured in duplicate using a portable electronic scale, accurate to the nearest 0.01 kg, calibrated daily using standard weights (Seca 334, Seca Corp., Baltimore, MD, USA).

Additional secondary measurements include length, cognitive and motor development and the prevalence and intensity of STH infections. Length (the recommended measurement of height in children < 30 months of age) will be measured in duplicate as recumbent crown-heel length on a flat surface using a measuring mat (Seca 210, Seca Corp., Baltimore, MD, USA), accurate to the nearest millimetre. Previous studies conducted by the proposed team in the Belén area showed inter and intra-rater reliability of over 95% for length/height and weight assessments (data not published), which are considered acceptable levels for anthropometric measurements. Cognitive and motor development will be assessed using the Bayley scale for cognitive and motor development (Bayley Scales of Infant and Toddler Development, Third Edition. Pearson Education Inc, Texas).

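### Secondary Z-score, underweight, stunting and Bayley comparisons leave out the child's own pre-randomization value, which costs precision but does not bias them

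*Protocol*

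**What the plan says.** The Secondary analyses section of the protocol names "derived weight indices (i.e. mean weight-for-age Z score and proportion of underweight), length (mean length gain, length-for-age Z score and proportion of stunting" and "cognitive and motor development (mean score) and STH prevalence and intensity". Length has a gain outcome. The Z scores, the two proportions and the Bayley scores are named as levels, with no reference to the 12-month value. The section does not name the visit; I read it as the 24-month visit.

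The tests are fixed: "Means will be compared using a one-way ANOVA procedure and proportions will be compared using chi-square statistics". Regression is conditional: "Adjustment for imbalances among measured determinants and risk factors will be conducted as needed".

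The Outcome measurements section shows that the missing covariate is available: "Prior to randomization, a baseline assessment will be conducted which will include anthropometry, and cognitive and motor development". All measurements are repeated at 18 and 24 months.

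Secondary analyses also plans linear and logistic models with baseline weight and length as interaction terms. Of these models the protocol says: "It will provide insight into both the preventive nature of deworming and also into whether deworming can reverse growth faltering".

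**The concern.** The primary outcome and length are analysed as gains from 12 months, which removes each child's starting point. The derived growth outcomes and the Bayley scores are compared as attained levels, with no planned use of that starting point. The Study community section reports that "The prevalence of underweight in children 12 to 14 months of age was recently estimated to be 31" per cent, so a sizeable share of children would enter already below the cut-off of -2 SD. Their status then adds variation to the 24-month comparison that no tablet could have caused.

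What is at stake is precision in the secondary outcomes. A modest real effect on Z scores, underweight, stunting or development could be reported with a wide interval and read as no effect, although the trial holds the data to estimate it better. Making adjustment depend on observed imbalance also leaves the choice of model until the data have been seen.

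**Working it through.** **1. The protocol's own figure.** The Sample size section gives 366 evaluable children per group for a 0.2 kg difference, SD 0.8 kg, 80% power, with Tukey correction over four groups. Alpha is not stated; I take 0.05 family-wise. The Tukey critical value is 3.633/√2 = 2.569, and

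n = 2 × (0.8/0.2)² × (2.569 + 0.842)² = 32 × 11.63 ≈ 373.

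This is within 2% of 366, so the same critical value is used for the Z scores below. No power is stated for the secondary outcomes.

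**2. Inputs.**
- Evaluable children per arm: 440 × 0.8 = 352 (Sample size section).
- Underweight at entry: 31% (Study community; an earlier local estimate, not trial data).
- Assumed, because the protocol gives neither: the 12-to-24-month correlation r, and a 0.2 Z effect with unit SD.

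**3. Variance relative to the attained level (= 1).** Equal variance at both visits is assumed. For a change score it is 2(1 − r); with the 12-month value as covariate it is 1 − r².

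| r | change score | 12-month covariate |
|---|---|---|
| 0.3 | 1.40 | 0.91 |
| 0.5 | 1.00 | 0.75 |
| 0.7 | 0.60 | 0.51 |
| 0.85 | 0.30 | 0.28 |

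The covariate helps at every positive r. A change score is less precise than the attained level when r is below 0.5.

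**4. Power for a 0.2 Z difference, one pair, Tukey critical value.** SE = √(2/352) = 0.0754.
- Attained level: 0.2/0.0754 = 2.653; 2.653 − 2.569 = 0.084; power 53%.
- Covariate, r = 0.3: 0.2/(0.0754 × √0.91) = 2.781; power 58%.
- Covariate, r = 0.5: 0.2/(0.0754 × √0.75) = 3.064; power 69%.
- Covariate, r = 0.7: 0.2/(0.0754 × √0.51) = 3.715; power 87%.
- Change score: 37% at r = 0.3, 53% at r = 0.5, 80% at r = 0.7.

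**5. How much 24-month underweight is carried over.** Take Z at 12 and 24 months as bivariate normal with unit SD, and mean −1.504 so that 31% lie below −2 at entry. With no drift in the mean, 58% (r = 0.6) to 80% (r = 0.9) of control-arm underweight at 24 months is in children already underweight at 12 months. With a drift of −0.2 Z the share is 54% to 71%.

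**6. Power for underweight, one pair, two-sided 0.05 without multiplicity correction.** In the no-drift model a 0.2 Z effect gives 31.0% v 24.3%.
- Unadjusted proportions: 51%.
- Logistic regression with baseline Z as covariate (600 simulated trials per setting): about 72% at r = 0.7, 75% at r = 0.8, 88% at r = 0.9.

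**7. Would incidence and recovery subsets do better?** About 352 × 0.69 = 243 children per arm would not be underweight at entry, and 352 × 0.31 = 109 would be. In the model of step 6, incidence has 38% to 50% power and recovery 28% to 49% (r = 0.6 to 0.9), against 51% for the pooled proportion.

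A purely preventive scenario favours incidence. With 70% persistence in both arms and new underweight cut from 20% to 12%:
- 0.31 × 0.70 + 0.69 × 0.20 = 35.5%
- 0.31 × 0.70 + 0.69 × 0.12 = 30.0%
- power about 35% pooled, 68% for incidence.

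If persistence also falls to 60% in the treated arm, its proportion is 0.31 × 0.60 + 0.69 × 0.12 = 26.9%. Power is then about 70% pooled, 68% for incidence and 34% for recovery. The subset advantage therefore comes from assuming no reversal effect.

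**The case against.** The strongest reply is that nothing is estimated wrongly. Under randomization, attained mean and mean change estimate the same group difference in Z. The main growth measures are already analysed as gains, the Z scores re-express the same weights and lengths, regression adjustment is allowed where needed, and a baseline covariate is the kind of detail often left to a SAP, which is not shown here. Most of this stands, and it limits the point to precision in secondary outcomes. It does not remove the point, because the protocol itself fixes unadjusted ANOVA and chi-square and makes adjustment depend on imbalance. The gain in precision exists whether or not the arms are imbalanced.

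A reader might also infer that the plan cannot tell new faltering from recovery. The documents do not support that. The pooled proportion alone cannot, but the same section plans linear and logistic models with baseline weight and length as interaction terms for this very question. Their cover is incomplete: as worded they use baseline size rather than underweight or stunted status, and they do not include the baseline Bayley score. That is a narrower gap than having no analysis at all.

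A third inference is that these outcomes should become change scores, or be split into incidence and recovery. Steps 3 and 7 show that neither is a general improvement.

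**Conclusion.** The point holds as a loss of precision. The secondary Z-score, underweight, stunting and Bayley comparisons are specified without the 12-month value that every child will have.

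The size depends on correlations that the protocol does not give. If Z scores correlate at 0.7 to 0.85 between visits, adjustment removes 49% to 72% of the variance. If Bayley scores correlate at 0.3 to 0.5, it removes 9% to 25%. The power figures further assume a 0.2 Z effect, unit SD and 352 evaluable children per arm. The underweight figures also rest on the 31% local estimate; no stunting prevalence at this age is given, so none was calculated for stunting.

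The documents do not support a claim of bias, nor a claim that prevention and reversal are left unexamined. The primary outcome and length gain are outside the point.

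**What to change.** In Secondary analyses, state that:
- 24-month weight-for-age Z, length-for-age Z, and Bayley cognitive and motor scores are compared between groups with the child's own 12-month value as covariate, not as change scores.
- 24-month underweight and stunting are compared by logistic regression adjusted for the 12-month weight-for-age or length-for-age Z score respectively.
- This adjustment is made whether or not an imbalance is seen.

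Keep the pooled proportions as outcomes, and keep the baseline weight and length interaction models for prevention versus reversal. Incidence among children not underweight or stunted at 12 months, and recovery among those who were, may be added as descriptive results only.

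The cost is wording, since all the values are already collected. One thing to note when reporting: the adjusted odds ratio is conditional on baseline Z and is not the same quantity as the crude odds ratio, so the raw proportions by arm should be shown beside it.

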### **Study population**

The study population will include children attending their routine 12-month CREDE visit (at which time measles vaccination is scheduled) in the study area. Using data provided by the Peruvian Ministry of Health, eight study health centres (“Centros de Salud”) have been identified in high-risk (i.e. high STH prevalence) areas neighbouring Iquitos. These include Centros de Salud: 1) 06 de Octubre, 2) 09 de Octubre, 3) Belén, 4) Cardozo, 5) Bellavista de Nanay, 6) Masusa; 7) 01 de Enero and 8) Fernando Lores.

The inclusion and exclusion criteria for participating children are as follows:

**Inclusion criteria:** 1) children attending any one of the eight study health centres for their 12-month CREDE visit (for feasibility and to ensure recruitment of children from highly STH endemic areas); 2) children living in or near the Belén, Punchana or San Juan district (to ensure recruitment of children from highly STH endemic areas, as well as to ensure high follow-up)

**Exclusion criteria:** 1) children who are attending the clinic for suspected STH infection (as they may require immediate, specific treatment); 2) children who have received deworming treatment

in the six months prior to randomization (as the effect of previous treatment may interfere with the effect of the randomized treatment); 3) parents planning to move outside of the study area within the next 12 months (to maximize participation rates and follow-up); 4) children under 12 months of age (as treatment is not recommended for this age group), or 14 months of age or older (to ensure participants are at a comparable growth and developmental stage); and 5) children with serious congenital or chronic medical conditions and who would be considered by the attending staff not to benefit from deworming.

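### The effect-modification model names baseline weight and length, not the planned age- and sex-standardised Z scores, so it measures faltering by a proxy partly mixed with sex

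*Protocol*

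**What the plan says.** All the relevant text on the model is in the protocol under Analyses, Secondary analyses.

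- **Aim of the model:** "To evaluate the possible modification of baseline anthropometry on the effect of deworming".
- **Modifiers:** multivariate regression, linear or logistic by outcome type, "with baseline weight and length included as interaction terms".
- **Purpose:** "This analysis is included to document the added value of deworming among young children who are already faltering". The text adds that the analysis should show whether faltering present by 12 months can be reversed.
- **Standardised measures in the same section:** "Length-for-age and weight-for-age Z scores will be calculated using the WHO Anthro software (Version 3, 2009"), with the comment "In addition to age, this method also takes into account the sex of the child".
- **Cut-offs for poor growth:** "WHO standards for underweight (<-2 SD), stunting (<-2 SD").

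The Study population section limits entry age by excluding "children under 12 months of age (as treatment is not recommended for this age group), or 14 months of age or older".

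Neither the Primary analysis nor the Secondary analyses section mentions a treatment-by-sex or treatment-by-age term. Covariate adjustment is for imbalances, as needed. The examples listed under Primary analysis do not include sex or age.

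**The concern.** Faltering means being light or short for one's age and sex. A low value in kilograms or centimetres is a different thing: a light child at entry may be undernourished, or may simply be a girl or one of the younger entrants. The protocol has the measure that separates these, explains what it corrects for and uses it for outcomes. It then names a different variable in the one analysis meant to find out what happens in faltering children.

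Two consequences follow. True modification by nutritional status is estimated through a noisier variable, so it is attenuated. And if the effect of deworming differed between boys and girls for any reason, part of that difference would appear as modification by weight. A report of greater benefit in lighter children could then not be cleanly separated from greater benefit in girls, which weakens any statement about preventing versus reversing faltering.

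**Working it through.** The protocol gives no figure for this analysis, so there is nothing to reproduce. The check asks how closely raw weight tracks the Z score and how much of a sex difference in effect leaks through. No separate calculation was made for length; the reasoning is the same.

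**Inputs from the protocol**
- Entry window: 12 to under 14 months, width W = 2 months (Study population).
- Mean weight gain on placebo: 2.0 kg over 12 months, so g = 2.0/12 = 0.167 kg per month (Sample size).
- SD of weight gain: 0.8 kg (Sample size).
- Children per group after 20% attrition: 440 × 0.8 = 352, or 704 in two groups (Sample size).

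**Assumptions not in the protocol**
- Boy-girl weight difference d: 0.3 to 0.8 kg.
- Within-sex, within-age SD of weight s: 1.0 kg.
- Sexes 50:50 and entry age uniform over the window.

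**Step 1: correlation of raw weight with Z.** Write raw weight as a sex difference plus growth with age plus s × Z. Then

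r² = s² / (s² + d²/4 + g²W²/12)

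The age term is 0.167² × 4/12 = 0.0093.

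| d (kg) | Variance of raw weight | r² | Information lost, 1 − r² |
|---|---|---|---|
| 0 (age only) | 1.0093 | 0.991 | 0.9% |
| 0.3 | 1 + 0.0225 + 0.0093 = 1.0318 | 0.969 | 3.1% |
| 0.5 | 1 + 0.0625 + 0.0093 = 1.0718 | 0.933 | 6.7% |
| 0.65 | 1 + 0.1056 + 0.0093 = 1.1149 | 0.897 | 10.3% |
| 0.8 | 1 + 0.1600 + 0.0093 = 1.1693 | 0.855 | 14.5% |

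A simulation of 2,000,000 children per row with d of 0.3 or more gives the same r² values. Over wider assumptions (d from 0 to 0.9 kg, s of 0.9 or 1.1 kg, g of 0.2 kg per month), r runs from about 0.99 down to 0.89. Age then explains 1% to 2% of raw-weight variance.

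**Step 2: effect on a true interaction.** Suppose the benefit changes by −0.20 kg per SD of Z, with d = 0.6, s = 1.0 and g = 0.2. The variance of raw weight is 1 + 0.09 + 0.0133 = 1.1033, its SD is 1.050, and r = 1/1.050 = 0.952.
- Expected slope per SD of raw weight: −0.20 × 0.952 = −0.190.
- Standard error with two groups of 352: √(2 × 0.8²/352) = 0.0603.
- z with raw weight: −0.190/0.0603 = −3.15. z with the Z score: −0.20/0.0603 = −3.32.

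A simulation of 400,000 children, rescaled to 704, gives −3.15 and −3.34.

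**Step 3: leakage from sex.** Suppose nutritional status does not modify the effect, and girls gain Δ = 0.2 kg more from treatment than boys. The expected slope on raw weight is −Δd/(4 × SD) = −0.2 × 0.6/(4 × 1.050) = −0.029 kg per SD, with z = −0.029/0.0603 = −0.47. The simulation gives −0.026 (z = −0.43) for raw weight and 0.002 for the Z score. With sex and age added as main effects only, the raw-weight slope stays at −0.026. With their interactions with treatment added, it falls to 0.0025.

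**The case against.** The strongest reply is that the protocol never says raw. It speaks of baseline anthropometry, gives no unit, and elsewhere in the section uses length as a group label that covers the Z score and stunting. A statistical analysis plan that is not at hand may fix the scale. This stands as a reason for caution, but it is not the natural reading: the section writes Z score where it means one, and the phrase that specifies the model does not. The point is also more than a detail left open, because the variable named does not match the purpose stated beside it.

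Several stronger readings are tempting, and the documents do not support them.

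- **That the model fails to test benefit in faltering children.** With r² between 0.86 and 0.97 under the assumptions, it does test it, with some loss.
- **That the group called light would be mostly girls.** Cutting raw weight at its lowest 31%, to match the underweight prevalence under Study community, would give 64% to 72% girls at differences of 0.5 to 0.8 kg. The plan makes no such cut. Its only weight cut-off is the WHO one.
- **That any sex difference in effect would show up as modification by weight.** Only part leaks. A 0.2 kg difference, as large as the trial's smallest meaningful difference, yields about −0.03 kg per SD, which could not be detected at this sample size. The protocol gives no reason to expect such a difference.
- **That age at entry matters much.** The narrow window makes its share small.
- **That weight and length enter one model together and obscure each other.** The text speaks of models in the plural and does not say this.

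It is also fair that covariates for these models are not listed exhaustively, so sex might be included. A main effect of sex would not remove the leakage, though; a treatment-by-sex term would be needed, and none is stated.

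**Conclusion.** The concern holds in a limited form. As worded, the effect modifiers are not standardised for age and sex, although the analysis is about faltering and the section defines poor growth by scores that are. The cost is about 3% to 15% of the information on the interaction for assumed sex differences of 0.3 to 0.8 kg and a within-sex SD of 1.0 kg. There is also partial leakage of any treatment-by-sex difference into the weight interaction. Both sizes rest on figures that the protocol does not give. The main harm is to interpretation; the loss of power is modest. This is a secondary analysis and the primary comparison of weight gain is untouched.

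**What to change.** In the Secondary analyses section, replace baseline weight and length as the interaction terms by baseline weight-for-age Z and baseline length-for-age Z from WHO Anthro. Keep both continuous and interact them with arm. Fitting one model per index and reporting the treatment effect at a few chosen Z values would help readers but is optional.

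The cost is one line of text. Weight and length are already measured at baseline and the software is already planned, so no new data are needed. Making the change before unblinding also removes a later choice between raw and standardised modifiers.

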### **Sample size**

Sample size calculations are based on the smallest meaningful difference in mean weight gain between intervention groups. From pilot data, we anticipate that the mean weight gain  $\pm$  standard deviation between 12 and 24 months in the group receiving usual care and placebo at both time points will be approximately 2.0 kg  $\pm$  0.8 kg. Based on previous research, we expect an improvement of 0.5 kg in weight gain in the group receiving deworming at 18 months of age (with 50% STH prevalence) compared to the group receiving usual care and placebo at both 12 and 18-month visits (i.e. 2.5 kg) and 0.7 kg improvement in weight gain in the group receiving deworming at both 12 and 18 months of age (i.e. 2.7 kg) [51]. This difference takes into account effect dilution based on treating groups of both infected children (who will benefit directly from the deworming treatment) and non-infected children (who may not benefit directly from the deworming treatment). The mean weight gain in those receiving usual care and deworming at the 12-month visit is estimated to be half of the gain in the group receiving usual care and deworming at 18 months of age (i.e. 2.25 kg).

In order to have 80% power to detect a difference in mean weight gain of 0.2 kg (the smallest meaningful difference we are aiming to detect), assuming a common standard deviation of 0.8, and using a one-way ANOVA which accounts for pairwise multiple comparisons using the Tukey correction, the estimated sample size per group is 366 children. Taking into account a 20% attrition rate after 12 months of follow-up, the required sample size is estimated to be 1760 children, or 440 children per group (MCG4 Software, Ohio University, 2008).

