### **Randomization and treatment allocation**

Computer-generated randomly ordered blocks of eight and twelve will be used to randomly allocate children to each intervention group. This will ensure a balance in the number of children assigned to each group. Randomization will be stratified according to health centre. Sequentially numbered large envelopes will be prepared to meet the estimated sample size. Each large

envelope will contain the assigned intervention for each recruited child. Inside this envelope will be two smaller envelopes with the same ID number: one which will contain the intervention to be administered to the child at 12 months of age and one which will contain the intervention at 18 months of age. One pharmacist and one clinician-scientist not otherwise involved in the study will prepare envelopes containing the randomly chosen group intervention assignment in advance. Each 'obstetriz' will have a supply of 12-month envelopes containing the random intervention assignments at baseline. Once the single-dose mebendazole or placebo tablet is administered at the 12-month visit, the now empty 12-month intervention envelope will be stapled to each child's questionnaire (along with the signed informed consent form). This material will then be stored together at the research office with the corresponding 18-month envelope (with the same ID number) until the 18-month follow-up (at which time the tablet in the 18-month envelope will be administered to that child). Envelopes will be distributed among the recruitment sites until the sample size has been achieved.

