### **Analyses**

#### *Primary analysis*

The results of the trial will be analyzed using an intention-to-treat approach. Following description of the study population at baseline, the mean weight gain between the first visit and the last follow-up (at the 24-month visit) will be compared between the four intervention groups using the one-way ANOVA procedure. While randomization should allow for approximately similar occurrence of determinants across the four intervention groups, adjustment for imbalances among the measured determinants and risk factors (e.g. history and duration of exclusive breastfeeding, timing of first introduction of complementary foods, home environment, family structure and characteristics and socioeconomic status) will be performed if needed using multivariate linear regression.

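### The primary ANOVA omits the stratifying health centre, and the only clustering remedy named is a logistic model, which does not fit the continuous outcomes

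*Protocol*

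**What the plan says.** - **Allocation** (Protocol, Randomization and treatment allocation): children are allocated individually in blocks of eight and twelve. "Randomization will be stratified according to health centre". Study population lists eight centres.
- **Primary outcome** (Outcome measurements): "The primary outcome will be the mean weight gain between the 12 and the 24-month visit". This is a continuous quantity in kg.
- **Primary analysis** (Primary analysis): mean weight gain "will be compared between the four intervention groups using the one-way ANOVA procedure". Linear regression follows only where measured determinants turn out to be imbalanced. Centre is not among the examples given.
- **Secondary outcomes** (Secondary analyses): these mix continuous measures (Z scores, length gain, Bayley scores) with binary ones (underweight, stunting, worm prevalence). The section twice assigns linear models to the continuous outcomes and logistic models to the dichotomous ones.
- **Clustering** (last lines of Secondary analyses): correlation within centres is to be examined through the intraclass correlation coefficient (ICC). Then: "If clustering is indeed detected, hierarchical logistic regression models will be used to obtain accurate estimates of treatment effects".

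**The concern.** Two things do not fit together.

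First, centre is built into the allocation but left out of the primary model. It can enter only through the adjustment for imbalance, which stratified blocks make unlikely for centre, or through the ICC check. Any variation in weight gain between centres then stays in the error term, although the design has already removed it from the treatment comparison.

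Second, the model named for the case where clustering is found is logistic, with no restriction on the outcomes it covers. A logistic model gives an odds ratio for a binary event and cannot give a difference in mean kg, cm, Z score or Bayley score. For the continuous outcomes the sentence cannot be carried out as written, and the protocol names no other clustering remedy. A statistical analysis plan would have to contradict the sentence to get this right.

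What is at stake is some precision on the primary comparison, and a clear instruction for the continuous outcomes.

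**Working it through.** **Inputs from Protocol, Sample size**
- Target: "In order to have 80% power to detect a difference in mean weight gain of 0.2 kg".
- SD: "assuming a common standard deviation of 0.8".
- Multiplicity: "using a one-way ANOVA which accounts for pairwise multiple comparisons using the Tukey correction", so six pairs among four groups.
- Stated result: "the estimated sample size per group is 366 children". Recruitment is 440 per group with 20% attrition, which leaves 440 × 0.80 = 352.

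**Assumptions**
- Alpha is not stated; I take 0.05 family-wise, two-sided.
- No ICC is given; I use 0.02, 0.05 and 0.10 as a range.
- Allocation is taken as balanced within centres.

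**Step 1. Reproduce the plan's figure.** The critical value for one pair is c = q(0.95; 4, df)/√2 = 3.637/1.4142 = 2.572. The standard error is 0.8 × √(2/n), and power comes from the noncentral t distribution with noncentrality 0.2/SE.
- n = 366: SE 0.0591, noncentrality 3.382, power 79.1%.
- Power reaches 80% at n = 373. The stated 366 is within 2% of that, so the setup is the plan's own.
- n = 352: SE 0.0603, noncentrality 3.317, power 77.2% with no centre effect.

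**Step 2. Effect of omitting centre.** With treatment balanced within centres, the between-centre part cancels from a treatment difference.
- True SE = 0.8 × √(1 − ICC) × √(2/352).
- The ANOVA without centre still reports 0.8 × √(2/352), so its intervals are too wide by the factor r = 1/√(1 − ICC).
- Its effective critical value is c × r. Per-pair type I error is 2 × P(t > c × r). Power uses threshold c × r and noncentrality 0.2/(true SE).
- With centre in the model, the threshold returns to c, with seven fewer error degrees of freedom (1,397 instead of 1,404).

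| ICC (assumed) | r | c × r | Per-pair error, centre omitted | Power, centre omitted | Power, centre included | Loss (points) |
|---|---|---|---|---|---|---|
| 0 | 1.000 | 2.572 | 1.02% | 77.2% | 77.2% | 0 |
| 0.02 | 1.010 | 2.598 | 0.95% | 77.4% | 78.2% | 0.8 |
| 0.05 | 1.026 | 2.639 | 0.84% | 77.7% | 79.7% | 1.9 |
| 0.10 | 1.054 | 2.711 | 0.68% | 78.4% | 82.2% | 3.9 |

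The losses are taken before rounding. Power without centre also rises with the ICC, because the true SE falls whether or not the model knows about centre.

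**Step 3. Check by simulation.** Eight equal centres, 366 per group, 6,000 runs per scenario. The type I error of the overall F test with centre omitted was 0.047, 0.040 and 0.036 at ICC 0.02, 0.05 and 0.10. With centre included it was 0.050, 0.048 and 0.051. The direction is conservative.

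**Step 4. The logistic sentence.** No arithmetic applies.

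| Outcome | Type | Model by the section's own rule | Model if clustering is found |
|---|---|---|---|
| Weight gain, length gain, Z scores, Bayley scores | Continuous | Linear | Logistic: no mean difference can be estimated |
| Underweight, stunting, worm prevalence | Binary | Logistic | Logistic: suitable |

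**The case against.** The strongest defence has four parts.

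- **Place and likely intent.** The clustering sentence closes the secondary analyses. The primary section fixes ANOVA, with linear regression for adjustment, and does not refer to the clustering step. Given the section's own rule on model types, the likeliest explanation is that the word linear was left out. This stands as an account of intent. It does not remove the need to correct a sentence that is the only clustering remedy and covers all outcomes as written.
- **Validity.** The ANOVA without centre is unbiased, keeps its error rate below nominal, and matches the method behind the sample size. This stands in full.
- **Adjustment list.** The examples for covariate adjustment are not exhaustive, so centre is not excluded. True, but it would enter only if judged imbalanced.
- **Detail for the analysis plan.** Fixed or random centre effects, and what counts as detected clustering, may be settled in a plan not shown here. I accept that and do not rest the point on a missing threshold.

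Three stronger readings are tempting and not supported. A reader might infer that weight gain would be dichotomised, with a large loss of power; the protocol defines no binary version of weight gain and no cut-point for it. A reader might infer that the primary comparison is definitely sent to a logistic model; the sentence's place under Secondary analyses does not establish that. A reader might infer that clustering by centre inflates false positives or calls for a design effect on the sample size; that applies when centres are randomised, whereas here children are randomised within centres.

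**Conclusion.** The point holds as a modest, low-cost correction, not as a threat to the validity of the primary result. The firmer part is textual: the logistic sentence is wrong as written for every continuous outcome and contradicts the rule stated in its own section. This part needs no assumption.

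The weaker part is efficiency. Leaving out the stratification factor costs under one point of power if the ICC is 0.02, and about four points if it is 0.10. These sizes rest on an assumed ICC range, an assumed alpha of 0.05, the protocol's SD of 0.8 kg, and 352 children per group after the planned attrition. Power at 352 per group is already a little under the 80% target, so precision that costs nothing to recover is worth having.

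**What to change.** 1. **Primary analysis:** fit a linear model for weight gain with intervention group and health centre as factors, specified from the outset. Keep the Tukey-adjusted pairwise comparisons.
2. **Secondary analyses:** include health centre in every model, not conditional on an ICC check. The ICC may still be reported descriptively.
3. **Clustering sentence:** reword it to name linear models for continuous outcomes and logistic models for binary outcomes, each with health centre included. If a hierarchical form is preferred, use the same split. The choice between fixed and random centre effects can be left to the analysis plan.

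The cost is about two sentences and seven degrees of freedom out of about 1,400 (4 × 352 = 1,408 children). No change to the sample size, allocation or data collection is needed.
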